# Use of drug therapy in the management of symptomatic ureteric stones in hospitalized adults (SUSPEND), a multicentre, placebo-controlled, randomized trial of a calcium-channel blocker (nifedipine) and an α-blocker (tamsulosin): study protocol for a randomized controlled trial

**DOI:** 10.1186/1745-6215-15-238

**Published:** 2014-06-20

**Keywords:** medical expulsive therapy, nifedipine, tamsulosin, ureteric stone

## Abstract

**Background:**

Urinary stone disease is common, with an estimated prevalence among the general population of 2% to 3%. Ureteric stones can cause severe pain and have a significant impact on quality of life, accounting for over 15,000 hospital admissions in England annually. Uncomplicated cases of smaller stones in the lower ureter are traditionally treated expectantly. Those who fail standard care or develop complications undergo active treatment, such as extracorporeal shock wave lithotripsy or ureteroscopy with stone retrieval. Such interventions are expensive, require urological expertise and carry a risk of complications.

Growing understanding of ureteric function and pathophysiology has led to the hypothesis that drugs causing relaxation of ureteric smooth muscle, such as the selective α-blocker tamsulosin and the calcium-channel blocker nifedipine, can enhance the spontaneous passage of ureteric stones. The use of drugs in augmenting stone passage, reducing the morbidity and costs associated with ureteric stone disease, is promising. However, the majority of clinical trials conducted to date have been small, poor to moderate quality and lacking in comprehensive economic evaluation.

This trial aims to determine the clinical and cost-effectiveness of tamsulosin and nifedipine in the management of symptomatic urinary stones.

**Methods/design:**

The SUSPEND (Spontaneous Urinary Stone Passage ENabled by Drugs) trial is a multicentre, double-blind, randomized controlled trial evaluating two medical expulsive therapy strategies (nifedipine or tamsulosin) versus placebo.

Patients aged 18 to 65 with a ureteric stone confirmed by non-contrast computed tomography of the kidney, ureter and bladder will be randomized to receive nifedipine, tamsulosin or placebo (400 participants per arm) for a maximum of 28 days. The primary clinical outcome is spontaneous passage of ureteric stones at 4 weeks (defined as no further intervention required to facilitate stone passage). The primary economic outcome is a reduction in the incremental cost per quality-adjusted life years, determined at 12 weeks. The analysis will be based on all participants as randomized (intention to treat). The trial has 90% power with a type I error rate of 5% to detect a 10% increase in primary outcome between the tamsulosin and nifedipine treatment groups.

**Trial registration:**

ISRCTN69423238; EudraCT number: 2010-019469-26

## Background

Urinary stone disease is very common, with an estimated prevalence among the general population of 2% to 3% and an estimated lifetime risk of 1 in 8 for white males [1] and 5% to 6% for white females [2], with men forming stones three times as often as women. Urinary stones often recur and the lifetime recurrence rate is approximately 50% [3]. The interval between recurrences is variable, with approximately 10% within 1 year, 35% within 5 years and 50% within 10 years [2]. The increased incidence of urinary stones in the industrialized world is associated with improved standards of living (mainly owing to the high dietary intake of proteins and minerals) and there is also an association with ethnicity and region of residence [4]. All urinary tract stones, and ureteric stones in particular, have a significant impact on patients’ quality of life. They are a common cause of emergency hospital admission due to severe pain with over 15,000 hospital admissions in England annually [5] using over 21,500 bed days. The pain leads to a requirement for analgesia, time off work and, often, repeated hospital admissions for therapeutic interventions.

A clinical guideline on the management of ureteric stones by the European Association of Urology and the American Urological Association [6] estimates that 68% of stones ≤5 mm and 47% of stones 5 to 10 mm in size can be expected to pass spontaneously and concluded that the majority of these stones pass within 4 to 6 weeks of presentation. Stones in the distal ureter pass more readily than stones located more proximally. The majority of the studies included in the guideline meta-analysis assessed stones in the distal (lower) ureter only. Consequently, patients with favourable features and with smaller stones in the lower ureter are traditionally treated expectantly. Those who fail standard supportive care (which involves analgesia, anti-emetics if nauseated, and intravenous fluids if there is associated vomiting), or who subsequently develop complications, undergo active treatment, such as extracorporeal shock wave lithotripsy, ureteric stenting, ureteroscopy with stone retrieval or *in-situ* lithotripsy, or percutaneous nephrostomy insertion. However, such interventions are expensive, require urological expertise and carry a risk of complications. For instance, extracorporeal shock wave lithotripsy is associated with up to 5% risk of sepsis and up to 8% risk of impaction of stone fragments causing urinary obstruction (‘Steinstrasse’), whilst ureteroscopy is associated with up to 4% risk of sepsis and up to 6% risk of ureteric injury [6].

In recent years, a growing understanding of ureteric function and pathophysiology has led to the hypothesis that drugs that cause relaxation of ureteric smooth muscle can enhance the spontaneous passage of ureteric stones [7-9]. The selective α-blocker, tamsulosin has specificity for α-1A and α-1D receptor subtypes [10,11], whilst other α-blockers variably block all α-1 receptor subtypes in a non-specific manner [12-14]. Similarly, calcium-channel blockers, such as nifedipine, inhibit ureteric smooth muscle contraction [15,16]. The use of both classes of drugs in augmenting the passage of ureteric stones has been termed medical expulsive therapy (MET) and this is proposed as a way to enhance stone passage and avoid the need for further intervention.

Two recent meta-analyses have reported the potential role of α-blockers and calcium-channel blockers in MET. Hollingsworth and co-workers [17] included nine randomized controlled trials, which included 693 subjects, although all but one trial had serious methodological flaws. Studied interventions included the calcium-channel blocker nifedipine and several different α-blockers whilst the comparative control arms included placebo, other vasodilators, antispasmolytics, anticholinergic therapy and corticosteroids. Overall spontaneous stone passage occurred in 47% of the control group whilst patients given MET with either drug were 65% more likely to pass the stone, with an absolute risk reduction of 31%. Three studies reported a head-to-head comparison between nifedipine and α-blockers. Two of these studies did not report any statistically significant difference in stone passage rates between the two drugs, whilst one study found the α-blocker to be superior to nifedipine, with a relative risk reduction of 26%.

In a more recent systematic review and meta-analysis, Singh and colleagues [18] included 22 studies; of which 13 assessed α-blockers, 6 assessed nifedipine, and 3 assessed both drugs against control. In the pooled analysis of 16 studies using α-blockers (*n* = 1,235), those receiving active treatment were 59% more likely to pass the stone, with a baseline stone passage rate of 50% in the control group. The incidence of mild adverse effects was 4%. The corresponding pooled result for nifedipine (nine studies, *n* = 686) showed that active treatment gave a 50% increased likelihood of stone passage, with an absolute risk reduction of 26%. The incidence of mild adverse effects was 15%. Both drugs significantly shortened, by between 2 and 6 days, the average time to stone expulsion [18]. However, the overall quality of the trials was poor.

In both meta-analyses, the majority of studies involved stones <10 mm located in the lower (distal) ureter. These two reviews both concluded that a large, high-quality randomized controlled trial is required to confirm their findings, suggesting that MET with either drug class can enhance spontaneous stone passage rate. In addition, several studies have previously reported that MET can significantly reduce the pain burden among patients in terms of reducing the frequency of pain episodes, pain severity and analgesic requirements.

However, more recent results provided by Bensalah and co-workers [19] appear to challenge the notion that α-blockers enhance spontaneous ureteric stone passage. The study, recently presented as an abstract, was a prospective, multicentre, randomized, double-blind, placebo-controlled trial, which evaluated the efficacy of tamsulosin versus placebo in patients with ureteric colic caused by distal ureteric stones. A total of 129 patients were treated for 42 days or until stone expulsion. At 42 days, there was no significant difference between the spontaneous expulsion rates between placebo (70.5%) and tamsulosin (77.0%; *P* = 0.41), nor in the mean stone passage times (10.1 and 9.6 days, respectively). Nevertheless, the overall mean stone diameter was 3.1 mm, which is smaller than all of the earlier studies included in the meta-analyses by Hollingsworth [17] and Singh [18]. The spontaneous stone passage rate in the placebo arm was high (70.5%) in comparison with other studies included in the two meta-analyses.

There is limited evidence on the cost-effectiveness of MET; an indirect cost-benefit analysis based on cost data from the USA and four European countries suggested that the use of tamsulosin could potentially result in a cost saving of US$ 1,132 per patient episode over conventional ‘watchful waiting’ [20].

In summary, the role of MET in reducing the morbidity and economic costs associated with ureteric stone disease is promising. The majority of clinical trials conducted to date have been small and of poor to moderate quality in terms of trial methodology or design. Furthermore, they have lacked a comprehensive economic evaluation. There is thus an urgent need for a definitive randomized controlled trial, such as that described in this protocol to inform the clinical management of patients with ureteric stone disease.

For the purposes of this randomized controlled trial, we have chosen to compare tamsulosin versus nifedipine. The weight of available evidence supports the use of tamsulosin as the α-blocker of choice in MET for ureteric stones. In the two previous reviews [17,18], tamsulosin was the agent of choice in 13 out of 16 randomized controlled trials. As discussed earlier, there also appears to be a theoretical advantage in using tamsulosin, owing to its specificity for the α-1A and α-1D adrenergic receptor subtypes. Similarly, the reviews also suggest that nifedipine should be the calcium-channel blocker of choice. The eight randomized controlled trials identified in Singh [17] and Hollingsworth [18] that examined the efficacy of calcium-channel blockers all used nifedipine. Nifedipine is also in widespread use in the UK’s National Health Service (NHS) for other indications.

The main anticipated risk to participants is that they suffer an adverse reaction to the trial medication. Treatment with α-blocker or nifedipine is associated with a small risk of adverse effects. In the report by Singh and colleagues [18], the incidence of mild adverse effects was 4% with α-blocker and 15% with nifedipine. However, both trial drugs are in common use for different indications, and the undesirable effects (such as postural hypotension and tachycardia) are well recognized. Patients with a contraindication to either drug will not be included in the trial. The off-label use of tamsulosin in women is well documented in the literature and there have not been any reports of any specific adverse reactions to treatment in female participants. However, the risks of tamsulosin use during pregnancy are unknown and nifedipine is contraindicated during pregnancy. Two suitable ‘highly effective’ forms of contraception must be used by women of childbearing potential entering the trial.

The aim of this trial is to determine the clinical effectiveness and cost-effectiveness of the use of tamsulosin and nifedipine in the management of symptomatic urinary stones. The potential benefits to participants are that the pain and discomfort caused by their ureteric stones will be relieved sooner and the avoidance of additional treatment (such as ureteroscopy or extracorporeal shock wave lithotripsy) will be reduced by 25% to 45%.

In the context of all trial groups receiving standard supportive care, two pragmatic comparisons will be made in evaluating MET for the facilitation of ureteric stone passage:

• Medical expulsive therapy (an α-blocker (tamsulosin) or a calcium-channel blocker (nifedipine)) versus placebo.

• An α-blocker (tamsulosin) versus a calcium-channel blocker (nifedipine).

The hypotheses being tested are:

1. The use of MET will result in an absolute increase in the spontaneous stone passage rate of at least 25% compared with placebo.

2. The use of an α-blocker (tamsulosin) will result in an absolute increase of 10% in the spontaneous stone passage rate compared with a calcium-channel blocker (nifedipine).

## Methods/design

This is a multicentre, double-blind, placebo-controlled, randomized trial evaluating two MET treatments (nifedipine or tamsulosin) versus placebo. The trial will be conducted in secondary care units with a high volume of admissions with ureteric stones across the UK. Figure 1 summarizes the trial design.

**Figure 1 F1:**
[figure not shown]
**Flow diagram of the SUSPEND trial.** CTKUB, Clinical tomography of the kidney, ureter and bladder; EQ5D, European Quality of Life, 5 Dimensions; NRS, numeric rating scale; SF36, Short Form (36) Health Survey.

### Inclusion and exclusion criteria

#### Inclusion criteria

• Patients presenting acutely with ureteric colic.

• Adults between 18 and 65 years of age (inclusive).

• Presence of stone already confirmed by non-contrast computed tomography of the kidney, ureter and bladder (CTKUB).

• Stone within any segment of the ureter.

• Unilateral ureteric stone.

• Largest dimension of the stone ≤10 mm.

• Women must be willing to use two methods of contraception listed in the protocol prior to the start of dosing until at least 28 days after receiving the last dose of trial medication, or they must be postmenopausal (defined as 12 months with no menses without an alternative medical cause) or permanently sterilized.

• Capable of giving written informed consent, which includes compliance with the requirements of the trial.

#### Exclusion criteria

• Women who have a known or suspected pregnancy (confirmed by a pregnancy test).

• Women who are breastfeeding.

• Asymptomatic incidentally found ureteric stone.

• Stone not previously confirmed by CTKUB.

• Stone with any one dimension >10 mm.

• Kidney stone without the presence of ureteric stone.

• Multiple (that is ≥ 2) stones within ureter.

• Bilateral ureteric stones.

• Stone in a ureter draining a solitary kidney (either anatomically or functionally).

• Patients with abnormal renal tract anatomy (such as a duplex system, horseshoe kidney or ileal conduit).

• Presence of urinary sepsis.

• Chronic kidney disease stage 4 or stage 5 (estimated glomerular filtration rate < 30 ml/min).

• Patients currently taking an α-blocker.

• Patients currently taking a calcium-channel blocker.

• Patients currently taking PDE5 inhibitors.

• Contraindication or allergy to tamsulosin or nifedipine.

• Patients who are unable to understand or complete trial documentation.

Women who are eligible to take part in the trial and are of childbearing potential (that is, are not postmenopausal (defined as 12 months with no menses without an alternative medical cause) or permanently sterilized) will be advised to use two forms of highly effective birth control (that is, results in a less than 1% per year failure rate) and continue use until at least 28 days after the last dose of trial medication. Acceptable forms of contraception include:

• Established use of oral, transdermal, injected or implanted hormonal methods of contraception.

• Placement of an intrauterine device or intrauterine system.

• Barrier methods of contraception: condom or occlusive cap (diaphragm or cervical or vault caps) in combination with a spermicidal foam, gel, film, cream or suppository.

• The woman’s sole male partner is sterile (with the appropriate post-vasectomy documentation of the absence of sperm in the ejaculate) before her participation in the trial.

• True abstinence, when this is in line with the preferred and usual lifestyle of the subject. Periodic abstinence (for example, calendar, ovulation, symptothermal, postovulation methods) and withdrawal are not acceptable methods of contraception for trial purposes.

### Trial interventions

Two active treatments will be investigated:

1. Tamsulosin, 0.4 mg/day up to a maximum of 28 days.

2. Nifedipine, 30 mg/day up to a maximum of 28 days.

### Identification and enrolment of potential participants

As standard practice, clinicians will assess patients presenting with suspected ureteric calculi. A log will be taken of all patients assessed, in order to document the reasons for non-inclusion in the study (for example, reason they were ineligible, declined to participate) to inform the CONSORT diagram. Following adequate pain relief and confirmation of ureteric calculi by CTKUB, eligible patients (according to the inclusion and exclusion criteria) will be provided with a patient information leaflet. The information leaflet will be given to each potential participant to explain the benefits and known drawbacks of all aspects of this trial. It shall specifically explain that the trial will investigate the effect of two different drugs against a placebo, and explain the likelihood of participants receiving each of the three trial treatments. A member of the local research team will identify whether the patient is interested in the trial and will ensure that any questions the patients have are answered appropriately. The patients will be given as long as they require, prior to discharge, to make a decision about whether or not to participate. Signed informed consent forms will be obtained from the participants in all centres, by an individual who is appropriately trained. On providing consent, the patient will be asked to complete a baseline questionnaire and will then be randomized to one of the three treatment groups. The participant’s permission will be sought to inform their general practitioner (GP) that they are taking part in this trial.

### Randomization and allocation

Eligible and consenting participants will be randomized to one of the two intervention groups or the placebo group on a 1:1:1 basis using the proven telephone interactive voice response randomization application hosted by the Centre for Healthcare Randomized Trials (CHaRT) and the Health Services Research Unit in Aberdeen. The randomization algorithm will use centre, stone size and stone location as minimization covariates. Upon randomization, the participant will be allocated a unique participant study number and assigned a numbered participant pack containing over-encapsulated trial medication to ensure that the participant, investigator and trial personnel remain blind to treatment.

### Code break or emergency unblinding

Participants will be given a patient card, which will have the study title, investigational medicinal product details, participant ID and out-of-hours contact details, in case of emergency unblinding. The treatment code should only be broken for valid medical or safety reasons, for example, in the case of a severe adverse event, where it is necessary for the principal investigator or treating healthcare professional to know which treatment the participant is receiving, to determine emergency treatment. Where possible, the members of the research team should remain blinded, subject always to clinical need.

In the event of a clinical emergency requiring unblinding, the first point of contact is the local research team where the participant was recruited to the trial. The participant will be given a card to carry with details of a contact telephone number at the site (for example, the number for the on-call urologist), to be used in the event that unblinding is necessary. Contact information will also be available in the participant’s hospital notes.

A member of the research team or a member of staff at the local recruiting site will telephone the CHaRT randomization service at the number provided using the trial centre ID and the participant study number (the trial ID number will be available from the patient card or the participant’s hospital notes). The name and position of the person making the call will be recorded. In the unlikely event of randomization service failure, the on-call pharmacist at Aberdeen Royal Infirmary will be contacted and the same procedure followed.

Following any unblinding via the telephone randomization service, automatic emails will be sent to the chief investigator, trial manager and members of the CHaRT Management team. Similarly, the on-call pharmacist will email the same list of people to inform them of any unblinding. These emails will not contain the treatment code and the trial team will remain blinded as far as is practicable.

The chief investigator will then ascertain why unblinding has taken place. If the participant was unblinded because of a serious adverse event, an SAE form will be completed and will be reported as stipulated below (Safety – Procedure for recording adverse events).

### Trial procedures

Participants will complete three questionnaires. The baseline questionnaire will be completed in hospital after entry into the trial (but before participants receive their study medication). Two further postal questionnaires, one at 4 and one at 12 weeks post randomization, will be sent from the co-ordinating office (CHaRT, Aberdeen). In addition, participants may be reviewed in clinic at approximately 4 weeks after randomization (as is common in routine NHS care). In the event that the participant does not return the questionnaire, a reminder letter will be sent out approximately 2 weeks later.

Three case report forms will be completed by the research team at the recruiting site, one at baseline and one at the follow-up visit (in the case of non-attendance, this form will completed from the participant’s notes). If participants indicate on the 12-week questionnaire that they have had further interventions since their 4-week questionnaire, a further case report form will be completed from the participant’s notes. Additionally if the participant fails to return the 12-week questionnaire a 12-week CRF will be completed from their medical records.

The complete trial processes are shown in Figure 2.

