#### Secondary

• Patient-reported: a reduction in the severity of pain as measured by a numeric rating scale [22,23]. Generic health profile will be measured by the SF 36 and the use of analgesia.

• Clinical: time to passage of stone; further interventions received at 12 weeks.

• Safety: participant-reported discontinuation of trial medications.

• Economic: NHS primary and secondary care use and costs up to three months, incremental cost per surgical interventions averted; modelled incremental cost per QALY beyond the 12-week trial follow-up.

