#### Timing and measurement of outcome assessment

Outcomes will be assessed at 4 weeks and 12 weeks post randomization, as shown in Table 1.

**Table 1 T1:** Source and timing of measures

**Outcome measures**	**Source**	**Timing**		
		**Recruitment**	**Post randomization**	
			**4 weeks**	**12 weeks**
Need for additional intervention	Case report form		×	×
Additional interventions received	Participant questionnaire and case report form		×	×
Pain (numeric rating scale)	Participant questionnaire	×	×	
Health profile and status (SF36, EQ5D)	Participant questionnaire	×	×	×
Use of analgesics	Participant questionnaire		×	
Adverse events	Participant questionnaire		×	×
Time to passage of stone	Participant questionnaire and case report form		×	×
NHS primary and secondary healthcare use	Participant questionnaire and case report form			×
Participant out of pocket costs	Participant questionnaire			×

EQ5D, European Quality of Life, 5 Dimensions; SF36, Short Form (36) Health Survey.

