#### Cost-effectiveness

The cost-effectiveness within the trial will be measured in terms of the number of participants needing further treatment during or at the end of the 12-week follow-up and the number of QALYs at 12 weeks. The number of QALYs will be estimated by combining estimated quantity of life, with quality of life derived from the EQ5D questionnaire (administered at baseline, 4 weeks and 12 weeks post randomization) and UK tariffs [28].

The within-trial analysis will be based on the 12-week follow-up and the results will be presented as the incremental cost per further treatments needed during or at the end of the 12-week follow-up and the incremental cost per QALY gained. The results will be presented as point estimates of mean incremental costs, number of further treatments needed, QALYs, incremental cost per further treatment needed and incremental cost per QALY. Measures of variance for these outcomes are likely to involve bootstrapping estimates of costs, number of further treatments needed, QALYs, incremental cost per further treatments needed and incremental cost per QALY. Incremental cost-effectiveness data will be presented in terms of cost-effectiveness acceptability curves. Forms of uncertainty, for example, concerning the unit cost of a resource from the different centres, will be addressed using deterministic sensitivity analysis. Where feasible, the results of the sensitivity analyses will also be presented as cost-effectiveness acceptability curves.

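### A participant who returns the 12-week questionnaire while still awaiting an intervention gets no 12-week case report form, the only source named for that need

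*Protocol article*

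**What the plan says.** All references are to the protocol article.

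- **Trial procedures, 4-week form.** Two CRFs apply to everyone: "one at baseline and one at the follow-up visit (in the case of non-attendance, this form will completed from the participant’s notes").
- **Trial procedures, 12-week form.** The third CRF is conditional. It is raised, from the notes, if participants report at 12 weeks that they "have had further interventions since their 4-week questionnaire, a further case report form will be completed". There is a second route: "Additionally if the participant fails to return the 12-week questionnaire a 12-week CRF will be completed from their medical records".
- **Trial procedures, late questionnaires.** The 4- and 12-week questionnaires are postal. If one is not returned, "a reminder letter will be sent out approximately 2 weeks later".
- **Table 1.** The row "Need for additional intervention" is scheduled at 4 and 12 weeks with the CRF as its only source. The separate row for interventions received draws on both the questionnaire and the CRF at both times.
- **Secondary outcomes.** The clinical list includes "further interventions received at 12 weeks".
- **Cost-effectiveness.** One within-trial effectiveness measure is the "number of participants needing further treatment during or at the end of the 12-week follow-up".

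**The concern.** The 12-week trigger asks about treatment that has already happened. Table 1 and the Cost-effectiveness section also want to know about treatment that is needed and has not happened. For a participant who returns the questionnaire, the procedure supplies the first and not the second.

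If that stands, the count of participants needing further treatment at the end of follow-up is too low, and the incremental cost per further treatment built on it is affected. At the planning rates, more participants fail to pass the stone on placebo than on either drug, so the number missed would probably be largest there and the absolute difference between arms on this measure would shrink.

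The second issue is the starting point of the trigger. The first follow-up CRF is tied to a clinic visit at about 4 weeks. The 12-week question looks back to a postal questionnaire that may come in later. A procedure between those two dates might have no CRF record of type and date.

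**Working it through.** The plan gives no figure on this point to reproduce, so the check is mainly a reading of the rules against each other.

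**1. Who gets a 12-week CRF, and what Table 1 then has for need at week 12**

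| Participant at week 12 | 12-week CRF? | Source for need at week 12 |
|---|---|---|
| Questionnaire not returned | Yes, from records | CRF |
| Returned, procedure reported since the 4-week questionnaire | Yes, from notes | CRF |
| Returned, no procedure, none needed | No | None |
| Returned, no procedure, one still needed or booked | No | None |

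The last two rows cannot be told apart from the source that Table 1 names. If absence of a form is read as absence of need, the fourth group is counted as not needing treatment. The Cost-effectiveness measure expressly includes need at the end of follow-up, so this group belongs in its count.

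A related uncertainty: the Discussion says that some 12-week questionnaires were short forms limited to the EQ5D. Such a form cannot report an intervention, and the document does not say whether its return counts as a return for the second trigger.

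**2. The starting point of the trigger**

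Take a participant seen on day 28, treated on day 35, who completes the reminded 4-week questionnaire on day 45.

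- The CRF, if filled in at the visit, predates the procedure.
- The 4-week questionnaire can report the procedure, because Table 1 has it collect interventions received.
- At 12 weeks the participant may truthfully answer that nothing has happened since that questionnaire, so no further CRF follows.

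The procedure is therefore known from self-report but may lack confirmation from the notes. This holds if the phrase refers to the date of completion. If it refers to nominal week 4, day 35 falls after the starting point, the CRF is triggered, and the window largely closes.

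**3. Size**

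With 400 per arm and the passage rates in the Sample size section (50%, 75% and 85%), expected non-passers are:

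- placebo: 400 × (1 − 0.50) = 200
- nifedipine: 400 × (1 − 0.75) = 100
- tamsulosin: 400 × (1 − 0.85) = 60

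These are roughly the pools from which unmet need at week 12 would come. The number missed in an arm is pool × u × r, where u is the share still needing treatment and untreated at week 12, and r is the share of those who return the questionnaire. The document gives neither u nor r, so no number follows.

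On direction: if the same share m of the true count is missed in every arm, each observed count is (1 − m) times the true one. The ratio between arms is then unchanged, and the absolute difference shrinks by the factor (1 − m).

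**The case against.** The strongest case on the other side has five parts.

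- **Non-responders are covered.** This is correct. The second trigger gives them a CRF from records, so the gap concerns responders only.
- **Interventions before a late questionnaire are not lost.** This is also correct. A reader might infer that procedures in weeks 4 to 6 vanish from the data. Table 1 does not support that, because the questionnaire is a named source for interventions received at both times, and 12-week NHS care use also draws on it. Only the CRF confirmation is at risk, and only on one reading of the trigger phrase. The questionnaire item itself is not shown.
- **The 4-week CRF already records need.** It does so at 4 weeks. It cannot show whether a need flagged then was still open at week 12, or whether one arose later. Table 1 schedules the item separately at 12 weeks for that reason.
- **Needing may be loose wording for receiving.** This is possible. The secondary clinical outcome is about interventions received, and the secondary economic outcome is about surgical interventions averted. But Table 1 keeps need and receipt in separate rows with different sources, and the economic measure includes the end of follow-up. If only receipt is meant, the text should say so.
- **An article condenses a fuller protocol.** That excuses omissions. Here the trigger, the source and the measure are all stated, and they do not fit together.

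**Conclusion.** The conflict among Trial procedures, Table 1 and Cost-effectiveness is real and needs to be reconciled. Among participants who return the 12-week questionnaire, anyone untreated but still needing or booked for an intervention has no source for the 12-week need item and would be undercounted. The late-questionnaire window is a secondary point about missing CRF confirmation, and it depends on the trigger phrase meaning the completion date.

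The size is unknown. A reader might put the missed share at 9% to 15% of interventions, by taking 30% to 50% of them to fall in weeks 4 to 6 and 30% of participants to reply late (0.30 × 0.30 = 0.09; 0.50 × 0.30 = 0.15). The document supports neither input, the share is the same in every arm by construction, and the self-reports would have to be discarded for those procedures to be lost. Nor does anything say that interventions are assigned to 4 or 12 weeks by the form they appear on rather than by their date, so misdating should not be inferred.

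The primary 4-week outcome is not affected: its follow-up CRF is completed for everyone, from the notes if the visit is missed. The exposure is confined to 12-week secondary and economic outcomes, so this is a correction worth making and not a threat to the trial's main conclusion.

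**What to change.** Preferred change:

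- Anchor the 12-week question to a fixed date: ask about any procedure for the stone since randomization, with dates.
- Ask in the same item whether any procedure is still awaited.
- Raise the notes-based 12-week CRF for every reported or pending intervention not already on a CRF, and keep the non-return trigger.

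If need at week 12 is not really wanted, the alternative is to restrict the 12-week need entry in Table 1 and the Cost-effectiveness measure to interventions received, so that the measure matches what the forms collect.

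The preferred change costs one reworded questionnaire item, a revised trigger rule and a modest number of extra CRFs completed from notes that the sites hold. The alternative costs only wording, but gives up information on treatment still pending at the end of follow-up.
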